### Randomization

An Interactive Web Response System (IWRS) will be used for electronic randomization of eligible patients. At the end of screening and prior to the first study RBC transfusion, the patient’s eligibility status will be entered into the study EDC system. If eligible, the patient will be randomized to receive either amustaline/GSH or conventional RBCs in a 1:1 ratio. Randomization will be stratified by site, baseline bleeding status (indication for RBC transfusion due to active bleeding or for anemia without active bleeding), patients’ participation in the optional extension period, and patients’ need for RCE (Fig. 2). Active bleeding will be defined as Grade 3 or 4 bleeding of the expanded WHO bleeding scale. Anticipated surgical bleeding and planned blood loss/replacement through RCE at baseline should be included as active bleeding (Grade ≥ 3) by definition.

### Transfusion support periods: 28-day acute transfusion support or 28-day + 6-month extension

Subjects will receive amustaline/GSH (Test) or conventional (Control) RBCs during the transfusion support period into which they have been enrolled, or until death, whichever is first. The day of the first study transfusion will be considered study Day 1 for defining the transfusion support period. Transfusions will be administered according to local institutional policy and safety standards as ordered by the medical team.

Data on all AEs, serious AEs (SAEs), transfusion reactions (TRs) and/or Unanticipated Adverse Device Effects (UADEs) will be collected from the initiation of the first study RBC transfusion through 28 days after the last study RBC transfusion. SAEs are required to be reported by the Investigator to the Sponsor or designee immediately (i.e., no more than 24 h after learning of the event). In an inpatient setting bleeding status and safety events will be collected daily following each study RBC transfusion until discharge or death, whichever is first. In the outpatient setting surveillance calls are to be completed at least monthly (at minimum every 35 days) if the subject is not seen by study staff for any other reason. If the monthly surveillance call interval coincides with a study visit, these data may be collected as part of the study visit assessments described in Tables 1 and 2.

For pediatric patients, the volume of the intended transfusion should be recorded. Study staff will record the proportion of the transfused unit. If for any reason a unit is not fully transfused, the percentage of the bag that was transfused (i.e., 75%, 50%, 25%) and the reason the remainder of the unit was not transfused or the why the transfusion was stopped will be recorded. This proportion will be recorded for each unit of study RBCs transfused and combined with the Hb concentration and net volume of the RBC component as measured by the blood center. These variables will be used to calculate the actual Hb mass transfused.

A negative antibody screen for amustaline/GSH RBCs should be confirmed prior to transfusing a patient with study RBCs and each time a standard of care ABO Type, Rh and screen (IAT) test is performed within the 28-day acute transfusion period and the 6-month extension period, if applicable.

The 28-day + 6-month extension period will include a subset of SCD patients who will receive three consecutive RCEs with study RBCs. For SCD patients undergoing regular RCE, the parameters listed in Table 2 should be assessed before and 15 min to 4 h after each RCE procedure. These assessments will be performed at 14-day (± 7 days) intervals between each of the 3 study RCE episodes.

Study RBC components will be ordered and administered to study patients by their treating physicians according to local standards of care. Randomized patients who do not receive any RBC transfusion within 28 days of randomization will be withdrawn and replaced. No additional data will be collected for these patients, who will not be included in the data analysis. These subjects may be reassessed for eligibility and re-enrollment after withdrawal.

If a subject is determined to have developed a treatment-emergent antibody to amustaline/GSH RBCs, the subject should be withdrawn from the active treatment phase of the study but should continue with all planned safety assessments per protocol. If the subject requires further transfusion, conventional RBC should be transfused. The subject should be actively investigated for signs or symptoms of intravascular or extravascular hemolysis for at least 4 weeks after the last study transfusion. Blood samples should be sent to the study’s central immunohematology reference center (Versiti Blood Center of Wisconsin, formerly Blood Center of Wisconsin) for assessment of the hemolytic potential and changing characteristics and titer of amustaline/GSH antibodies every 1–2 weeks for 4 weeks or until resolution of the event.

### 28-day (± 7 days) post-transfusion support follow-up period

Day 1 of the 28-day (± 7 days) follow-up period is the first day after the last study transfusion. The last study transfusion will occur no later than the end of the 28-day acute transfusion period or the 6-month extension period. For subjects enrolled in the 6-month extension period, the last study transfusion may also be the tenth transfusion episode for repeated simple transfusion subjects, or the third RCE episode in SCD subjects. At least one monthly surveillance call will be performed with all subjects to collect data on AEs, SAEs, TRs and UADEs during the 28-day (± 7 days) follow-up period. On Day 28 (± *7* days) after the last study transfusion, subjects will return to the study site for the following assessments: Vital signs, AEs, SAEs, TRs, comorbid conditions, blood samples for safety labs (hematology, blood chemistry, and coagulation panels), IAT and DAT, and immune reactivity to amustaline/GSH RBCs. Samples may be used for additional in vitro research testing as required to confirm transfusion-transmitted pathogen mediated infections.

For SCD patients undergoing regular RCE, the assessments described in Table 4 should be collected on Day 28 (± *7* days).

**Table 4 Tab4:** Laboratory Assessments for SCD Subjects Enrolled in the RCE Arm

• Hematology panel• Reticulocytes • Proportion (%) of HbS, HbA, and HbF • Coagulation panel • Plasma frozen sample for determination of S-300 and GSH concentrations	

### Day 75 (± 15 days) end-of-study visit

On Day 75 (± 15 days) of the follow-up period after the last study RBC transfusion, a blood sample will be collected for a DAT and an immune reactivity test for antibodies specific for PR-RBCs.

### Patient withdrawal criteria

Study patients are free to withdraw consent and discontinue/withdraw from the study at any time without prejudice to further treatment. A patient’s participation in the study may be withdrawn at any time at the discretion of the Investigator if he/she feels it is in the patient’s best interest.

Upon early termination or withdrawal of patients who have received at least one study RBC transfusion, the tests required during the Day 28 (± 7 days) and/or Day 75 (± 15 days) visits will be performed. If this is not possible then, depending upon the study period in which the patient was withdrawn, a physical examination and standard laboratory tests should be performed; other blood samples should be collected (as needed); and data on concomitant medications and AEs should be obtained.

### Enrollment pauses and stopping rules

The study may be temporarily paused or definitively stopped based on poor or slow subject accrual or for safety recommendations from the Data Safety Monitoring Board (DSMB).

A delayed serologic transfusion reaction (DSTR), delayed hemolytic transfusion reaction (DHTR), acute hemolytic transfusion reaction (AHTR), or hyperhemolysis syndrome in subjects exposed to study RBCs may result in individual patient withdrawal, enrollment pause, or a clinical stop. All subject recruitment, enrollment, randomization, transfusion and clinical follow-up activities will stop during a “clinical stop.” In certain cases, enrollment or transfusion of study patients may be resumed after a stop with the authorization of the DSMB and/or FDA. Subjects will continue to receive non-study conventional RBCs during a clinical stop, as needed. All safety monitoring activities will continue per protocol during a clinical stop.

### Sample size

The study was originally designed to enroll ~ 600 subjects to allow 95% probability that any AEs that occurs at a 1% rate would be documented in subjects that are bleeding or non-bleeding at baseline. With the later amendments to include patients undergoing chronic transfusions including RCE, the total enrollment target was increased to 600–800 enrolled subjects for the primary safety endpoints. The primary safety endpoint will be assessed in the modified intention-to-treat (mITT) population that receive at least one study RBC transfusion, a subset of the enrolled subjects. The primary efficacy endpoint will be assessed in the subset of the mITT that was non-bleeding at baseline, as active bleeding confounds the assessment of Hb increment. At least 352 non-bleeding evaluable patients (approximately 174 per treatment group) will allow for 80% power to declare non-inferiority for the primary efficacy endpoint treatment difference with a non-inferiority margin of 15% of the control mean at the two-sided 0.05 alpha level, assuming no true treatment difference and a coefficient of variance (CV) of 50%. Under the same assumptions, 468 non-bleeding evaluable subjects (234 per treatment group) will provide 90% power.

The study will also aim to enroll one-hundred-and-forty 28-day + 6-month extension subjects, including up to 30 SCD patients requiring regular repeated RCE to allow a total of three consecutive RCE procedures in at least 20 transfused evaluable patients to provide experience with repeatedly transfused subjects. Between 600 to 800 randomized subjects will be enrolled to meet the sample size targets to power the primary efficacy endpoint and the 28-day + 6-month extension period enrollment goals.

### Blinding

Clinical staff and others caring for participating patients, as well as the Sponsor (and delegates), will be blinded to treatment assignment. Unblinded delegates will monitor the production of study RBC components at designated blood centers and distribution at hospital transfusion centers. Only appropriate blood bank and transfusion service staff will be able to access the treatment arm assignment. Study RBC component labels will be indistinguishable for Test and Control products. In order to protect the blind, the final products (Test and Control) will be transferred into an FDA approved RBC storage container (Fenwal™ Transfer Pack™ Container – 600 mL, product code 4R2023) using a sterile docking technique. This transfer will occur on the day of each planned study transfusion.

### Data management

Patients’ medical records are considered the source data. Study data will be recorded on electronic case report forms (eCRF) stored in a 21 CFR Part 11-compliant electronic data capture (EDC) system selected by the Sponsor and maintained by a third-party vendor (InForm, Oracle, Austin, TX, USA). Batch production records and data reports from the blood centers’ electronic data management systems may be considered source data for processing study RBC components. Source data will be verified against the EDC system by the Sponsor and/or by a contract research organization (CRO) selected by the Sponsor (Precision for Medicine, Carlsbad, CA, USA). All study documents will be entered into an electronic trial master file (TMF) maintained by the Sponsor.

### Confidentiality

Individual patient medical information obtained as a result of this study is considered confidential, and disclosure to third parties other than those described below is prohibited. Data generated as a result of this study are to be available for inspection upon request by local health authority auditors, the Sponsor’s monitors, or by a participating site’s IRB/IEC.

### Study coordination and management

Routine study management (including oversight of external partners and contract research organizations, as needed) will be conducted by the Sponsor through a team of Clinical Research Associates and Medical Monitors led by a Clinical Trial Manager and supervised by the head of Clinical Research and the Chief Medical Officer. The study team will hold routine (often daily) interactions with study sites and external partners, as needed, as well as regularly scheduled weekly, monthly and quarterly study review meetings.

## Outcomes

### Primary and secondary endpoints

The primary safety endpoints include the proportion of subjects with any TEAEs possibly, probably or definitely related to a study RBC through 28-days after the last study transfusion, and the proportion of subjects with treatment-emergent antibodies with confirmed specificity to PR-RBCs. The primary efficacy endpoint is the adjusted Hb increment averaged over multiple transfusions for all non-bleeding subjects at baseline, defined as the difference between pre- and 15-min-24 h post-transfusion Hb values divided by the total Hb content transfused during each transfusion episode.

Secondary efficacy and safety endpoints will include:Adjusted Hb consumption defined as total Hb mass transfused (g) divided by body weight (kg) and the duration of the study transfusion period (days) in patients without active bleeding at baseline.HbA clearance in SCD patients undergoing regular RCE.All TEAEs for 28 days after last study transfusion.Transfusion reactions related to study RBCs (as defined by the CDC National Healthcare Safety Network [NHSN] Hemovigilance Module protocol), for 28 days after the last study transfusion.Treatment-emergent immunization to RBC alloantigens.All-cause mortality through 28 days after the last study transfusion.

Secondary Safety Endpoints (for SCD patients undergoing RCE):Proportion of subjects with adverse events of special interest (AESI) through 28 days after the last study transfusion.S-300 and GSH plasma levels before and 15 min to 4 h after RCE.

### Statistical methods

Only patients in the mITT analysis set will be included in the efficacy analysis. Non-study RBCs received during the study transfusion period will be included to calculate the total Hb content transfused for the two efficacy endpoints in the mITT analysis set. Patients receiving non-study RBC transfusions as their first study transfusion will be excluded from the Per Protocol (PP) analysis set and only those transfusions that occur before a non-study transfusion will be analyzed. Data from the initial 28-day period and the optional 6-month extension period will be summarized together and separately.

Treatment difference in non-bleeding mITT patients will be assessed using a non-inferiority test with a pre-specified non-inferiority margin (15% of the Control mean value), stratified by site. An analysis of variance (ANOVA) model will be used to estimate and test the treatment effects while controlling for the clinical site. Non-inferiority will be declared if the lower bound of a 2-sided 95% confidence interval for the mean treatment difference (Test—0.85 × Control) is greater than or equal to zero.

For the primary efficacy endpoint, the adjusted Hb increment will be averaged over one or more transfusion episodes. An episode-specific Hb increment will be calculated by subtracting the Hb value before each transfusion episode from the Hb value taken 15-min-to-24-h after each transfusion episode. The relatively long post-transfusion assessment period is justified by prior findings that post-transfusion hemoglobin increments are not meaningfully impacted by the timing of the samples collected between 15 min and 24-h post-transfusion [14, 15]. Increments will be adjusted by the Hb content transfused in each given episode (which may contain multiple RBC components). The Hb content of each transfused RBC component will be calculated using the Hb concentration and post-sample weight of the RBC component (both measured at the blood center), and the percentage of the unit transfused (assessed at the hospital). The Hb mass of each transfusion episode is the sum of the Hb content for all RBC components transfused.

The Hb content transfused (g) for a study RBC component will be calculated as:$$post sampling weight \left(g\right)\div 1.06 \left(\frac{g}{mL}\right)\times percent of unit transfused \times hemoglobin concentration (g/mL)\div 100$$

Non-study RBCs received during the study transfusion period will be included in the calculation of Hb content transfused. For each non-study RBC component received, the Hb content will be imputed using the average Hb content per study RBC component from the Control group within each clinical site.

The treatment difference in the adjusted Hb increment will also be summarized descriptively (with a 95% confidence interval) as exploratory analyses for the following mITT subgroups:Repeatedly transfused non-bleeding patients (defined as non-bleeding patients who receive at least 3 study RBC episodes).Subgroup by clinical site, age group (< 18, 18–64, and ≥ 65 years old), sex, and race (e.g., white vs. other races), as appropriate.

For SCD patients enrolled in the 6-month extension for three RCE procedures, HbA clearance will be estimated from the area under the curve (AUC) calculated by the trapezoidal rule based on measurements from samples collected within 4-h of each RCE, on Day 14 (± 7-days) and prior to the next scheduled RCE. Values will be adjusted by the duration in days used to calculate the AUC (i.e., between the 15 min-to-4-h post-transfusion sample and pre-transfusion sample of the next transfusion) and averaged over all study RCE procedures for each patient.

For the secondary efficacy endpoint of Hb consumption, the analysis will be conducted only in non-bleeding mITT patients who participate in both of the initial 28-day and 6-month extension periods and will utilize integrated data from both periods. Treatment differences in non-bleeding mITT patients will be assessed using the same non-inferiority test methods described above for the primary endpoint analysis. Interaction terms between the treatment and covariates will be explored, as necessary. For the adjusted Hb consumption analysis, the upper bound of a two-sided 95% confidence interval for the treatment difference (Test – 1.15 × Control) less than or equal to zero will result in the rejection of inferiority null hypothesis and the conclusion of non-inferiority.

Adjusted Hb consumption will be calculated as total Hb mass transfused in grams divided by body weight in kg at baseline and duration of the study transfusion period in days (g/kg/day). The total Hb mass transfused is the sum of the Hb content for all study and non-study RBC components transfused during the study transfusion period (i.e., 28 days or 28-day + 6-months, unless subjects prematurely discontinue the study).

For patients who prematurely discontinue from the study, the duration of the study transfusion period will be calculated as:

$$\left(end\;date\;of\;study\;transfusion\;period\right)-\left(start\;date\;of\;first\;study\;RBC\;component\right){+1}$$

Where the end date of the study transfusion period will be defined according to the following rules:For subjects who withdraw due to death, the date of death will be the end date of the study transfusion period.For patients withdrawn for reasons other than death (e.g., lost to follow-up, withdrawal of consent, AE), the last date of a study or non-study RBC transfusion during the planned study transfusion period (28-days or 28-day + 6-months) will be the end date of the study transfusion period.

The treatment difference in the adjusted Hb consumption will also be summarized descriptively as exploratory analyses for the following mITT subgroups:Repeatedly transfused non-bleeding patients (defined as non-bleeding patients who receive at least 3 study RBC episodes).Subgroup by clinical site, age group (< 18, 18–64, and ≥ 65 years old), sex, and race, as appropriate.

Only mITT patients will be included in the safety analysis. Treatment-emergent AEs are defined as AEs with an onset date/time that is on or after the start date/time of the first study RBC transfusion. AEs will be summarized by treatment group, system organ class (SOC), and preferred term as applicable. The proportion of patients with AEs possibly, probably, or definitely related to study RBC transfusion will be compared between treatment groups using a Cochran-Mantel–Haenszel (CMH) test (controlling for clinical site and baseline bleeding status). The risk difference associated confidence interval will also be reported. In the event of sparse counts, Fisher’s exact test may also be used to provide statistical interpretation.

To investigate the potential impact of irradiation, subgroup analysis by irradiation status (yes vs. no) may be presented for the primary efficacy endpoint and selected safety data (including SAEs, AEs, and potassium level).

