^4^Medications administered during anesthesia for surgical or other procedures are not collected

^5^The date of non-study RBC transfusion, if any, during the 28-day follow-up period and 6-month extension, if applicable, must be documented

^6^Daily for inpatients when available through the end of the acute transfusion period for inpatients

^7^Performed in conjunction with every routine standard of care test for ABO Type, Rh and screen (IAT) test that is performed during the Acute Support Period

^8^If, during the acute support period or follow up assessments (Day 28), a positive DAT result is observed, participating sites will follow their routine standard practice for confirmation/characterization of DAT positive samples; this should only apply to any conversion from a negative to a positive DAT after enrollment, that is not part of an investigation of hemolysis or of a positive IAT with evidence of an amustaline/GSH RBC antibody, in which case further investigations may be appropriate after discussion with the sponsor

^9^Hematology Panel: WBC, RBC, Hb, Hct, MCV, MCH, MCHC, MPV, RDW, PLT, Neutrophil %, Monocyte %, Lymphocyte %, Basophil %, Eosinophil %

^10^Blood Chemistry Panel: BUN, Creatinine, EGFR, NA, K, GLU, Cl, CO_2_, TP, ALB, ALKP, AST (SGOT), ALT (SGPT), LDH, CPK, TBIL, DBIL

^11^Coagulation Panel: PT, INR, APTT, Fibrinogen

^12^In the outpatient setting if the subject is not seen by study staff for any other reason, surveillance calls are to be completed at least monthly (at minimum every 35 days) to collect AEs, SAEs, TRs, and UADEs starting from the initiation of the first study transfusion through the entire transfusion support period and through 28 days after the final study transfusion. If the monthly surveillance call interval coincides with a study visit, data will be collected at the study visit

**Table 2 Tab2:** Schedule of Enrollment, Interventions, and Assessments: 28-Day Plus 6-Month Extension for Sickle Cell Disease Patients Undergoing Red Cell Exchange (RCE) Patient population: Sickle Cell Disease patients on a regular, repeated RCE program receiving 3 consecutive RCE procedures. Note: Pre-allocation screening and randomization steps are the same as those in Table 1. The footnote numbering scheme in this table also maps to Table 1

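### The primary Hb-increment ANOVA leaves out the pre-transfusion Hb that the trial already collects: a valid analysis that gives up a modest amount of precision

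*Protocol article*

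**What the plan says.** The Statistical methods section of the protocol article builds the endpoint in three steps. An episode increment is obtained by "subtracting the Hb value before each transfusion episode from the Hb value taken 15-min-to-24-h after each transfusion episode". It is divided by the grams of Hb given in that episode. Then "the adjusted Hb increment will be averaged over one or more transfusion episodes", which leaves one value per subject.

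The model for that value is named: "An analysis of variance (ANOVA) model will be used to estimate and test the treatment effects while controlling for the clinical site". Non-inferiority is declared if the lower 95% limit for Test − 0.85 × Control is at or above zero. No section enters pre-transfusion Hb into this model. Covariates are mentioned only in the paragraph on the secondary endpoint, Hb consumption, and none is named there.

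The baseline value exists. Table 1 schedules the hematology panel at screening and before each transfusion episode, and its footnote lists the contents: "Hematology Panel: WBC, RBC, Hb, Hct" and further items. The endpoint cannot be calculated without a pre value.

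The Sample size section takes no credit for a covariate. It works with the raw spread of the endpoint, "assuming no true treatment difference and a coefficient of variance (CV) of 50" percent, and "with a non-inferiority margin of 15% of the control mean at the two-sided 0.05 alpha level".

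**The concern.** Subtracting the pre value is not the same as adjusting for it. Measurement and hydration error in the pre sample enters the increment with the opposite sign, so a change score is normally negatively correlated with its own starting value. Subtraction fixes the slope on the pre value in advance, whereas a covariate lets the data estimate it. Dividing by grams transfused rescales the difference but does not remove this dependence.

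Two things are at stake. Variance that baseline Hb could explain stays in the residual, so the interval that decides non-inferiority is somewhat wider than necessary. And if the arms happen to differ in starting Hb, the unadjusted estimate carries part of that difference. The Randomization section stratifies by site, bleeding status, extension participation and need for red cell exchange, but not by starting Hb.

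**Working it through.** **Inputs.** Margin 0.15 and SD 0.50, both in units of the Control mean; true difference 0; two-sided alpha 0.05 (Sample size section). The group size is 176 (Abstract), which is half of 352. The Sample size section prints about 174 per group beside the same total; 176 is used here.

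**The plan's own figure.** n per group = 2 × [0.50 × (1.960 + 0.842) / 0.15]² = 174.4, so 175 per group or 350 in total, against 352 stated. The noncentral t version gives exactly 176. For 90% power the same formula gives 234 per group (468), as stated. Power at 176 per group = Φ(0.15 / (0.50 × √(2/176)) − 1.96) = Φ(2.814 − 1.96) = 80.4%. The design reproduces with no covariate.

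**With baseline Hb.** Let r be the size of the within-site correlation between the averaged, dose-normalized increment and the first pre-transfusion Hb. The residual SD becomes 0.50 × √(1 − r²). The documents do not give r, so it is an assumption:

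| r | variance removed (r²) | total N for 80% | power at 176 per group |
|---|---|---|---|
| 0 | 0% | 350 | 80.4% |
| 0.1 | 1% | 346 | 80.7% |
| 0.2 | 4% | 336 | 81.9% |
| 0.3 | 9% | 318 | 83.9% |
| 0.5 | 25% | 262 | 90.1% |

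The last row only shows what a higher correlation would bring; nothing in the documents supports it.

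**Rough guide to r.** For a plain single change score with equal pre and post SDs and pre/post correlation ρ, r = −√((1 − ρ)/2). Assumed values of ρ of 0.9 and 0.8 give −0.22 and −0.32. The trial's endpoint is not a plain change score, so this is only a guide.

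**Dilution by averaging.** Error in the first pre value enters only the first of k increments. With independent episodes (assumption) the correlation falls to r/√k. A value of 0.30 for one episode becomes 0.30/√3 = 0.17 for three, or 3% of the variance.

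**The decision contrast.** For Test − 0.85 × Control with equal SDs the variance factor is 1 + 0.85² = 1.7225 instead of 2. Power at 176 per group is then 85.8% unadjusted and 88.9% at r = 0.3.

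**Chance imbalance.** The between-arm difference in baseline Hb has a standard error of √(2/176) = 0.107 SD. An imbalance of 1.96 standard errors is 0.21 SD. It moves the unadjusted estimate by r × 50% × 0.209, which is 1.0%, 2.1% or 3.1% of the Control mean at r = 0.1, 0.2 or 0.3, against a margin of 15%.

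**The case against.** The strongest reply is that nothing here is wrong. A site-adjusted ANOVA of one value per subject is unbiased under 1:1 randomization, and its confidence interval already allows for chance imbalance on average over randomizations. The sample size uses the raw CV, so design and analysis agree. That stands. The protection at issue is conditional: it concerns the imbalance that actually occurs.

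The second reply is that the gain is probably small. The site term already absorbs between-site differences in starting Hb where local transfusion policy drives them. Dividing by grams adds variation unrelated to baseline, and averaging dilutes the correlation in the repeatedly transfused subjects whom the trial deliberately recruits. One common slope for single- and multi-episode subjects is also only approximate. All this stands, and it is why the range is kept to 0.1 to 0.3.

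The third reply is that the SAP, not shown here, may list more covariates. The article, however, names the primary model outright, and its passing mention of covariates belongs to the secondary endpoint and does not name baseline Hb.

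The last reply is that enrollment has closed, so replacing the primary model now is a late change. This is a real cost, but the Discussion says the study is still blinded, so the change can be made credibly.

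A reader might infer that the ANOVA is biased, that the trial is underpowered, or that about a quarter of the subjects could have been saved. The documents support none of these. The first two fail on the points above. The third needs a correlation of 0.5, for which the documents give no basis.

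**Conclusion.** The point holds as a modest, low-cost improvement and not as an error. The stated analysis is valid, and 80% power is reached without the covariate. Adding first pre-transfusion Hb would raise power at 176 per group by 0.3 to 3.5 percentage points (from 80.4% to between 80.7% and 83.9%) if the within-site correlation lies between 0.1 and 0.3. It would also limit a conditional shift of about 1% to 3% of the Control mean under an unlucky baseline imbalance. These sizes rest on the assumed correlation, the plan's CV of 50%, no true difference and normal approximations. Below a correlation of 0.2 the power gain is under 2 points; only a correlation above the assumed range would make it large.

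**What to change.** Before unblinding, prespecify the primary model as an ANCOVA with treatment, site and the Hb measured before the first study transfusion. Do not use later pre-episode values as covariates, because they follow randomized treatment and may be affected by it.

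Form Test − 0.85 × Control from the adjusted means at the overall mean baseline Hb, and state this in the plan. The two weights do not sum to zero, so the baseline term does not cancel from the contrast and its value depends on where the means are evaluated.

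Keep the site-only ANOVA as a sensitivity analysis.

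The cost is one degree of freedom in about 352 subjects and a documented, dated change to the analysis plan made while the study is blinded. It needs no new data and no more subjects.
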